## Abstract

**Background:**

Urban Indigenous populations face disproportionate mental health challenges, including high rates of posttraumatic stress disorder, depression, and substance use disorders, yet they have limited access to health services, especially culturally relevant care. The mechanism for providing care to Indigenous people in the United States, the Indian Health Service, is significantly underfunded and only accessible to certain Indigenous people. With more than 70% of Indigenous individuals in the United States living in urban settings, there is a growing need for innovative health care solutions. A community-based, Indigenous-led health and mental health–focused nonprofit in the northeast United States developed ShockTalk, a tele–mental health linkage-to-care app tailored specifically for Indigenous communities, to fill this gap.

**Objective:**

This study aims to assess (1) the feasibility, including accessibility, experience, and value, of ShockTalk for practitioners and clients interested in providing or receiving culturally responsive mental health treatment, and (2) changes in client attitudes related to tele–mental health treatment value and trust in ShockTalk technology.

**Methods:**

This study outlines the development and pilot study of ShockTalk. The conceptual framework is based on the behavioral model of health care use. ShockTalk uses artificial intelligence to connect clients with Indigenous or culturally aligned therapists and facilitates access to care via Facebook Messenger. Using a prewaitlist or postwaitlist design, 5 client participants will be admitted to the study at first, and 5 additional participants at 3 months. Data collection includes presurveys and postsurveys on client attitudes toward mental health treatment and trust in the ShockTalk platform at baseline and a 3-month follow-up, followed by in-depth qualitative interviews at 3 months. A preliminary economic evaluation will track direct costs (ie, therapist time, platform fees, and administrative expenses) and compare relative costs across treatment doses. Analyses will assess the feasibility of data collection and inform a future full-scale trial.

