## Methods

### Overview

To test the feasibility of ShockTalk among Indigenous clients, we will conduct a small pilot study with 10 Indigenous therapy-seeking clients and 3 Indigenous mental health practitioners in Lenapehoking. This study was designed as a preliminary feasibility pilot to inform a larger trial and, therefore, was not prospectively registered.

After informed consent and baseline assessment, clients will be randomly allocated 1:1 to immediate access to ShockTalk (treatment) or to a 3-month waitlist control (5 clients per arm). The allocation list will be generated by a study team member not involved in enrollment and uploaded to a centralized randomization module, which will reveal the assignment only after baseline data entry. Allocation events will be logged. In the absence of a centralized system, sequentially numbered, sealed opaque envelopes prepared from the same allocation list will be used.

All participants will complete baseline surveys and a 3-month follow-up survey (3 months postrandomization). Waitlist participants will be offered access to the linkage-to-care intervention 3 months after their initial baseline survey is completed. Qualitative data collection at 3 months from baseline will include 1-hour semistructured interviews (Multimedia Appendix 1) with a purposive subsample of 5 clients (selected to reflect a range of engagement and experiences across arms) and a single focus group with participating practitioners. Finally, a preliminary cost analysis will be conducted using data from both arms to assess the feasibility of cost data collection and to generate exploratory cost estimates across varying levels of engagement. Analyses will be descriptive and feasibility-focused (ie, recruitment, retention, acceptability, and data completeness); inferential effectiveness claims will not be made given the pilot sample size.

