### Measures

#### Quantitative Measures

The first survey instrument will examine changes in attitudes related to tele–mental health treatment value for clients before and after treatment facilitated by ShockTalk. One month before treatment and 3 months after treatment, clients will be given the Attitudes Toward Seeking Professional Psychological Help-Short Form survey [24]. This survey measures participants’ openness to seeking professional help for emotional problems and the value and need for seeking professional help. Clients are asked whether they disagree, partly disagree, partly agree, or agree with an item, including questions such as, “The idea of talking about problems with a psychologist strikes me as a poor way to get rid of emotional conflicts” and “A person with an emotional problem is not likely to solve it alone; he or she is likely to solve it with professional help.” Their attitudes toward seeking professional help are scored based on the sum of all responses. The short version of the scale demonstrates internal consistency ranging between 0.82 and 0.84, and high test-retest reliability (a=0.80) [24]. Once the presurveys and postsurveys are collected, the study team will examine the differences in openness to treatment before and after ShockTalk*.* A positive difference between the pretreatment and posttreatment Attitudes Toward Seeking Professional Psychological Help-Short Form score will indicate an increase in client valuation of mental health care treatment. *t* tests (1-tailed) will be used to evaluate whether the differences are statistically significant.

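### The attitude survey has two incompatible schedules, so waitlist clients supply either an untreated change or a before/after-treatment change, but not both

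*Protocol article*

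**What the plan says.** **Entry and allocation.** The abstract's Methods paragraph names a waitlist design and says "5 client participants will be admitted to the study at first, and 5 additional participants at 3 months". It says nothing about how clients are allocated. The Methods Overview is explicit: "After informed consent and baseline assessment, clients will be randomly allocated 1:1 to immediate access to ShockTalk (treatment) or to a 3-month waitlist control", with "5 clients per arm".

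**Survey timing.** The Overview anchors the surveys to randomisation: "All participants will complete baseline surveys and a 3-month follow-up survey (3 months postrandomization". It adds: "Waitlist participants will be offered access to the linkage-to-care intervention 3 months after their initial baseline survey is completed". The abstract also places the surveys "at baseline and a 3-month follow-up, followed by in-depth qualitative interviews at 3 months". Ethical Considerations pays for two surveys, one at baseline and one at 3 months. Quantitative Measures gives a different anchor for the attitude scale: "One month before treatment and 3 months after treatment, clients will be given the Attitudes Toward Seeking Professional Psychological Help-Short Form survey". It then defines the quantity of interest as the difference in scores before and after ShockTalk, to be tested with one-tailed t tests.

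**Interview timing.** The Overview holds client interviews 3 months from baseline, in a subsample drawn across arms. Qualitative Measures holds them 3 months after treatment participation.

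**The concern.** In a waitlist trial, time from randomisation and time from treatment differ between the arms by the length of the wait, here 3 months. A schedule tied to one clock therefore gives the waitlist arm different data from a schedule tied to the other. The article uses both clocks for the same instrument.

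The conflict settles two things: whether the study has an untreated comparison at all, and what a waitlist client's change score means. The attitude scale is also the primary outcome of the exploratory effectiveness part of the cost analysis, and Limitations and Future Research says that the findings will feed sample size and power calculations for a later randomised trial. Pooling untreated changes with post-treatment changes would blur any such use. Data completeness, one of the feasibility measures in the Overview, cannot be scored without knowing when each survey was due.

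The interview conflict has a practical side. The client interview asks people to walk through using ShockTalk and to compare the therapy it led to with earlier therapy. Waitlist clients interviewed 3 months from baseline are only then being offered access.

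**Working it through.** The plan has no power calculation to reproduce: the article gives no significance level, power, effect size or standard deviation. Two consistency checks are possible.

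- Clients: 5 + 5 = 10, which agrees in the abstract and the Overview.
- Payment (Ethical Considerations): 2 surveys × US $10 + 1 interview × US $30 = US $50, the stated total. The total closes with exactly two surveys, so no third survey is described that could serve both purposes.

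Next, each stated schedule is laid over each arm's access date.

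**Inputs**
- Immediate arm: access at month 0 (Overview).
- Waitlist arm: access at month 3 after baseline (Overview).
- Schedule A (Overview): surveys at months 0 and 3 from randomisation.
- Schedule B (Quantitative Measures): surveys at treatment start − 1 month and treatment start + 3 months.
- Assumptions: baseline and randomisation fall on the same date, treatment starts at access, and the 3 months in schedule B run from the start of treatment.

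**Schedule A, expressed as time from access (survey month − access month)**
- Immediate: 0 − 0 = 0 and 3 − 0 = +3, a before/after pair.
- Waitlist: 0 − 3 = −3 and 3 − 3 = 0, an untreated 3-month change with nothing after access.

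**Schedule B, expressed as months from baseline (access month − 1, access month + 3)**
- Immediate: 0 − 1 = −1 and 0 + 3 = 3. The first survey would precede baseline by a month, which fits poorly with immediate access after baseline.
- Waitlist: 3 − 1 = 2 and 3 + 3 = 6, a before/after pair with no untreated 3-month change.

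| Schedule | Waitlist surveys (months from baseline) | Before/after-treatment pairs | Untreated 3-month changes |
|---|---|---|---|
| A, from randomisation | 0 and 3 | at most 5 of 10 | 5 |
| B, from treatment | 2 and 6 | up to 10 of 10 | 0 |

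**Sensitivity to the assumptions.** If the 3 months in schedule B run from the end of a 3-month treatment period, the waitlist surveys fall at months 2 and 3 + 3 + 3 = 9. If treatment starts some time after access, both waitlist surveys move later by that amount. Neither changes the count in the last column: schedule B has only one survey before treatment, and one observation cannot give an untreated change.

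**The abstract's entry sentence.** If it is read literally, the second five clients enter at month 3 and have no observation in months 0 to 3, so again there are 0 untreated change scores. If it means that five get access first and five get access 3 months later, it agrees with the Overview.

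**The case against.** The strongest reply is that there is one design with one stray sentence. The abstract, the Overview and Ethical Considerations all describe a baseline survey and a 3-month follow-up, and only Quantitative Measures departs from that. This is fair. It makes the Overview schedule the likelier intention, and it means that the article does not set out a complete second design. But the stray sentence sits in the section that defines the attitude outcome and its test, so it cannot be disregarded.

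A reader might infer from the abstract that groups were formed by order of entry, without randomisation. The documents do not support that. The abstract is silent on allocation, its sentence opens by naming a waitlist design, and being admitted to the study may be loose wording for being given access. The Overview describes 1:1 allocation from a list made by someone not involved in enrolment and revealed only after baseline data entry. What stands is an ambiguity to clear up.

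A waitlist arm without a survey after crossover is also a common choice and no error in itself. It matters here only because Quantitative Measures asks for a difference before and after ShockTalk and does not limit it to one arm.

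Finally, the study is a pilot. The Overview says that analyses are descriptive and that no inferential effectiveness claims will be made, and Results reports data collection finished with 4 clients enrolled. So no efficacy decision depends on this, and the counts out of 10 describe the planned sample. The enrolment figure does not remove the problem: readers of the results still need to know whether those 4 clients were randomised and when they were surveyed.

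**Conclusion.** The concern holds as an internal contradiction in the timing of the attitude survey, with a matching contradiction in interview timing. With two surveys per client, the waitlist arm can give an untreated control change or a before/after-treatment change, but not both. In the planned sample, the randomisation-anchored schedule leaves 0 of 5 waitlist clients with a post-access survey and before/after pairs in at most 5 of 10 clients. The treatment-anchored schedule leaves 0 untreated 3-month changes and so no control.

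This rests on waitlist access at month 3 and on the two surveys that the payment total implies. It does not depend on whether the 3 months after treatment are counted from its start or its end. The treatment-anchored timing is stated for the attitude scale only; the article gives no such timing for the trust items. The abstract's entry sentence is a secondary point of clarity and is not evidence of non-random allocation. The text is wrong as written and should be corrected before or with the results, because the correction changes what the attitude outcome means.

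**What to change.** State one entry scheme and one survey and interview anchor in the abstract, the Overview, Quantitative Measures and Qualitative Measures, matching what was actually done for the 4 enrolled clients.

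- **If the Overview was followed:** in Quantitative Measures, time the attitude scale at baseline and 3 months after randomisation in both arms. Label the waitlist month-3 survey as the untreated control observation. Restrict the before/after ShockTalk difference and its t test to the immediate-access arm, and do not pool the arms. Reword the abstract so that the second five are waitlisted and not newly admitted at month 3. Re-anchoring the survey without restricting the contrast is not enough, because waitlist clients would still have no post-access survey.
- **If entry was in fact staggered, or surveys were timed from treatment:** remove the randomised-control description and report an uncontrolled pre/post study.

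For the later trial, if both contrasts are wanted, waitlist clients need a further survey after their access period.

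For this study the cost is a text correction with no new data. The downside is that either fewer clients contribute to the before/after contrast (at most 5 of the planned 10) or the claim to a control group is lost.

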**Results:**

This study was funded in April 2022. Data collection occurred between May 2022 and October 2024. In total, 4 client participants and 2 therapist participants were enrolled. Data analysis is complete and results are expected to be published in February 2026.

**Conclusions:**

This pilot study will offer insights into optimizing technology-based, culturally relevant mental health care. By examining varying levels of engagement and associated costs, this research seeks to identify the most effective and cost-efficient strategies for improving mental health outcomes in urban Indigenous populations in the United States. ShockTalk has the potential to shape future health care innovations in this field. Findings are expected to contribute significantly to Indigenous mental health care by offering insights into sustainable, accessible, and culturally appropriate telehealth interventions, guiding future policy and practice.

**International Registered Report Identifier (IRRID):**

DERR1-10.2196/67757

## Introduction

### Background

We use the term *Indigenous*, which does not center on arbitrary geopolitical lines, to describe American Indian, Native American, and Alaskan Native populations in what is now known as the United States. Urban-living Indigenous people experience disproportionately higher rates of mental health disorders [1,2], often as a result of forced isolation from their homelands of origin, communities, and a lack of adequate mental health care resources [3,4]. The most significant mental health concerns facing urban Indigenous communities include a high prevalence of substance use disorders [5], depression, suicide, anxiety [6], and posttraumatic stress disorder (PTSD) [2]. For example, estimates of rates of PTSD among Indigenous people range from 16% to 24% [7-9], which is 3 times the rate of lifetime PTSD among the general population [10], and rivals the lifetime rate (29%) among US veterans returning from Iraq and Afghanistan [11].

### Access to Mental Health Services

Addressing the mental health disparities among Indigenous communities that reside in urban contexts presents unique challenges. The Indian Health Service (IHS), created in 1955 through Public Law 568, The Transfer Act of 1954, exists to fulfill the US government’s treaty obligations and legal responsibilities to provide health care to Native American and Alaska Native tribes [12]. The IHS is currently funded at less than half of its required budget [13] and faces significant challenges, including barriers to service, staffing shortages, extended wait times, and diminished access to quality care [14]. Notably, the IHS dedicates only 1% to 2% of its line budget to urban Indian health programs, which are funded only through contracts, and many of these programs have limited capacity [15]. Due to colonial policies, such as the termination, boarding school, and relocation eras, many Indigenous community members have been displaced from their original homelands into urban areas [16]. As a result, more than 70% of Indigenous people, specifically those identified as American Indian or Alaska Native, in the United States today live in urban areas [17], of which only 25% live within an IHS service area [15]. The discrepancy between the location of Indigenous medical services and the areas in which most Indigenous individuals in the United States live poses a significant challenge, highlighting the need for health care innovation.

Furthermore, the rates of health insurance coverage are markedly lower for Indigenous people compared with those for non-Hispanic White individuals, compounding this health disparity. As of 2019, just over half (51.9%) of Indigenous individuals alone or in combination had private health insurance coverage [6]. The percentage of Indigenous people who were enrolled in Medicaid or other public health insurance coverage was 42.9%, and 14.9% of Indigenous individuals did not have health insurance coverage; the comparative rates for non-Hispanic White individuals were 74.7%, 34.3%, and 6.3%, respectively [6]. Therefore, there is a profound need to improve and expand systems of care to help urban Indigenous individuals access affordable mental health treatment.

### Telehealth and Indigenous Populations

Telehealth, or telemedicine, uses two-way, real-time telecommunication audio and video technologies, such as computers, tablets, or smartphones, to deliver health care services and public health [18]. Telehealth interventions allow health care providers to meet with patients remotely to diagnose, consult, treat, educate, and manage care, and they also allow patients to manage their care [19]. Implementing care and interventions among underserved populations through telehealth has been shown to be feasible and cost-effective [20], with the ability to be culturally tailored to meet the needs of Indigenous populations [21]. In a recent scoping review regarding telehealth use by Indigenous populations from Australia, Canada, New Zealand, and the United States [21], 47% of the 321 studies identified used mobile health (mHealth), and 26% focused on mental health. Indigenous communities expressed concerns regarding privacy and confidentiality, limited broadband internet, uncertainty in their ability to use the technology, and lack of trust in the therapeutic relationship. However, collaboration with Indigenous communities to develop and implement the intervention and offer Indigenous health care providers or cultural liaisons (13%) in its delivery indicated an increase in cultural safety. Notably, none of the identified studies discussed interventions that served solely as a linkage to mental health care or facilitated a way for Indigenous clients to identify mental health support.

With these goals in mind, this manuscript provides a detailed protocol for the feasibility pilot of the first tele–mental health linkage-to-care app tailored specifically for Indigenous communities, named ShockTalk. The purpose of the telehealth app is to improve access to culturally relevant mental health care for Indigenous individuals. The following section outlines the conceptual framework, the process of development for the mobile app, and identifies the needs of community members.

### Conceptual Framework

The proposed research is informed by the behavioral model of health care use [22], which aims to understand how health care use and health-related outcomes are influenced by predisposing, enabling or inhibiting, and need factors at both the individual and contextual (eg, community and policy level) characteristic levels. Individual and contextual factors also influence personal health practices and care processes. In an iterative cycle, outcomes affect subsequent predisposing and enabling factors, the perceived need for health services, and health behavior.

Figure 1 depicts the conceptual framework of this study. The variables shown in black font will be included in our preuse and postuse survey. Guided by these findings, primary data collection and analysis of in-depth interviews will seek to better understand the components of the conceptual model in gray font (eg, process of medical care). This study focuses on the relationship between *individual characteristics* and subsequent *health behaviors*.

**Figure 1 figure1:**
[figure not shown]
Conceptual framework for the ShockTalk pilot study. PTSD: posttraumatic stress disorder.

### Preliminary ShockTalk App Development

ShockTalk was conceptualized by 3 New York City–based Indigenous individuals with experience in social work, public health, technology, and research. To better understand the barriers to and facilitators of culturally responsive mental health service access in urban areas for Indigenous individuals, 70 in-depth interviews with self-identified Indigenous individuals were conducted by the community-based partner team who originally conceptualized this app with community members and mental health clinicians in the urban area of Lenapehoking (specifically, in what is now known as New York City). The findings of this assessment are presented in Table 1. Finances, lack of insurance, and lack of systems to help Indigenous clients identify culturally appropriate service providers were identified as the most prominent barriers through qualitative analyses. Facilitators of care included sliding-scale service offerings and connections to Indigenous service providers or health care providers that match the client on other statuses or identities.

**Table 1 table1:** Themes from the preliminary ShockTalk development.

Theme	Findings
Structural barriers to accessing therapy	Perceived stigma of accessing therapy Need for variety of therapeutic settings, online, in person, and “meet the client where they are” Lack of availability of Indigenous therapists Access to therapy, including telehealth Limited scheduling and availability, and a cumbersome process
Interpersonal barriers to accessing therapy	Lack of comfort with the therapist Uncertainty about online therapy Fear of not having a cultural connection Cost Lack of spiritual component in Western-dominant therapy
Characteristics of an ideal therapist	Ability to connect deeply with someone “beyond the surface” who is “down to earth” Relational (ie, compassionate and lets the person talk) vs advice giving Can assure privacy and trust, especially in a small community Shared characteristics and understanding of experience Shared understanding of trauma and colonization Understanding of Indigenous culture, experiences, and ways of knowing Share Native or Indigenous identity who better understand the “everyday struggle” connected with Indigenous identity History of working with Indigenous people “in a good way” Feel connected Can offer cultural or spiritual coping mechanisms and tools

